**All participants**

Study participants must be adults ≥ 18 years old with capacity to give informed consent and to comply with the study design. All participants must be living in Scotland, be registered with a GP within NHS Scotland, and must have fluency in written or spoken English.

**BD Lithium participant group**

Participants in the ‘BD Lithium’ group must have a diagnosis of bipolar disorder according to DSM V criteria, confirmed with the Structured Clinical Interview for DSM5 (SCID) with at least one previous manic or two previous hypomanic episodes. Where possible, the diagnosis of bipolar disorder will be corroborated using clinical notes or records. Participants in the ‘BD Lithium’ group must be clinically euthymic with no episodes of depression, hypomania or mania for at least three months prior to enrolment. Participants will be asked to inform the study team of any mood episodes they have developed in the three months prior to any study appointment. Affected appointments will be rescheduled once the participant has been euthymic for 3 months. They must be on a stable lithium medication regimen for at least six months prior to study participation.

**BD Non-Lithium participant group**

Participants in the ‘BD Non-Lithium’ group must have a diagnosis of bipolar disorder according to DSM V criteria, confirmed with the Structured Clinical Interview for DSM5 (SCID) with at least one previous manic or two previous hypomanic episodes. Where possible, the diagnosis of bipolar disorder will be corroborated using clinical notes or records. Participants in the ‘BD Non-Lithium’ group must be clinically euthymic with no episodes of depression, hypomania or mania for at least three months prior to enrolment. Participants will be asked to inform the study team of any mood episodes they have developed in the three months prior to any study appointment. Affected appointments will be rescheduled once the participant has been euthymic for 3 months.

Participants in the ‘BD Non-Lithium’ group must not be currently taking lithium, and must have no lithium use for at least six months prior to study participation.

**
*3.6.3 Exclusion criteria*
**

**All participants**

Exclusion criteria for all participants includes the inability to give consent and inability to comply with study design. Individuals cannot participate in the study if they are currently enrolled in an interventional research study. Medical exclusion criteria include: pregnancy, diagnosis of sleep or circadian disorders; claustrophobia; epilepsy; blindness or significant visual impairments; existing eye disease such as glaucoma or age-related macular degeneration; previous surgery on the retina; use of melatonin or melatonin-suppressing medications (such as beta-blockers). Other significant medical conditions which, in the investigator’s opinion, could skew or confound data from investigations (e.g. neurological conditions such as multiple sclerosis) will be assessed on a case-by-case basis and excluded if necessary. Individuals with harmful use of or dependence on psychoactive substances, including alcohol (as per ICD-10) will not be eligible to participate. Due to their impacts on circadian rhythmicity, current shift work (variable day shift pattern or night shifts) and trans-meridian travel within the preceding month exclude individuals from participation.

**Control participant group**

Participants in the control group must not have recent history of any psychiatric illness or psychotropic medication use (within the past 12 months for psychiatric condition), or previous history of severe mental illness (psychosis, severe depression, psychiatric hospital admission). First-degree family history of psychosis or severe mood disorder excludes individuals from participation.

**
*3.6.4 Participation window*
**

The amount of time each participant will be actively participating in the study will vary depending on how closely together they wish to complete all parts. The anticipated minimum amount of time required will be 20 months, from receipt of study invite to completion of all assessments.

**
*3.6.5 Payment of Study Participants*
**

All enrolled study participants will be reimbursed for their participation time, costed at £15 per hour (estimated 38 hours total). If a participant withdraws from the study, they will be paid for the time they have completed up until that point. Travel (public transport, fuel, parking) and childcare costs will additionally be reimbursed. If a participant completes all of the assessments, they will be reimbursed up to a maximum of £750 including expenses. Payments will be made via bank transfer using University of Edinburgh standard procedure.

**
*3.6.6 Withdrawal of Study Participants*
**

Participants will be informed via the PIS that their participation is entirely voluntary and that they are free to withdraw from the study at any time. Information already collected will still be used when preparing the results of the study, unless the participant tells us they don’t want their information to be used in this way. Once the study has finished and the data have been analysed for publication, participants will no longer be able to withdraw their information. If a participant lost capacity during the study, it would not be appropriate to continue the study data collection as ongoing consent would be required. Data already collected would still be used. To safeguard rights, minimal personally identifiable information will be collected.

**
*3.6.7 Risk assessment and distress procedure*
**

The research team will have regular contact with participants in this study. If any significant issues arise, all participants will be informed by phone and letter. This includes both self-reported issues and issues that may arise from the tests conducted, or data collected. Some participants may find some questions in the questionnaires sensitive in nature (questions about their mental health past and present). Where there is any clinical risk to the participant (for example the disclosure of suicidal thoughts) the interviewing psychiatrist or research team member will ask for consent to contact the patient’s GP and treating community mental health team (if they have one), so that appropriate monitoring and follow-up can be arranged.

### 3.7 Study assessments

Table 1 details provides an overview of all study assessments and time points at which they will occur. Further details of the assessments are as follows:

**Table 1. T1:** Study Assessment measures and collection time points. Abbreviations: AUDIT, Alcohol Use Disorders Identification Test; DSM-V, Diagnostic and Statistical Manual of Mental Disorders 5
^th^ Edition; EEG, electroencephalography; OCT, Optical Coherence Tomography; OCT-A, Optical Coherence Tomography Angiography; m-SPAQ, Modified Seasonal Pattern Assessment Questionnaire; MCTQ, Munich Chronotype Questionnaire; VEPs, Visual Evoked Potentials.

Assessment	Screening Call	Baseline Clinical Assessment	Part A	Part B	Part C
1. Collection of contact details					
2. Verbal informed consent					
3. Assessment of Eligibility Criteria					
4. Written informed consent					
5. Demographic and lifestyle data					
6. Alcohol Use Disorders Identification Test, AUDIT					
7. Past psychiatric history (including medical notes screening if possible)					
8. Assessment of past and current medication use					
9. Retrospective Assessment of the Lithium Response Phenotype (Alda) Scale					
10. Pittsburgh Sleep Quality Index (PSQI) questionnaire					
11. Munich Chronotype Questionnaire (MCTQ)					
12. Modified Seasonal Pattern Assessment Questionnaire (m-SPAQ)					
13. WHODAS 2.0 Questionnaire					
14. Sleep Diary					
15. 24-hour actigraphy					
16. Measurement of light exposure levels					
17. Pregnancy test (if applicable)					
18. Heart rate, blood pressure, height and weight measurements					
19. Cannulation					
20. Blood sample collection					
21. Ingestion of eCelsuis telemetric temperature pill					
22. Overnight Sleep Study Protocol					
23. Bilateral ocular application of pupil dilator medication Minims Tropicamide 1.0%					
24. 30 minute light stimulus					
25. Follow-up wellbeing call					
26. Cambridge Colour test					
27. Contrast sensitivity test					
28. Colour discrimination test (Just noticible differences)					
29. Pupillometry					
30. Electroencephalography (EEG)/ Visually evoked potentials (VEPs)					
31. Fundus camera photograph					
32. Ultra-widefield scanning laser ophthalmoscopy					
33. Optical coherence tomography (OCT)					
34. OCT Angiography (OCT-A)					
35. Optical Biometry					
36. Automated perimetry					
37. Autorefraction					

**3.7.1.1
Screening Appointment
**

**1.**
* Collection of contact details*: Contact details will be collected during the initial screening appointment to allow for further communications between the research team and potential participants.

**2.**
* Verbal informed consent*: Potential participants will provide verbal informed consent for the purposes of the screening call data collection.

**3.**
* Assessment of eligibility criteria*: Potential participants will be screened for eligibility criteria at the initial screening day and again at baseline study visit. This will include a structured diagnostic assessment for bipolar disorder at the screening appointment.

**3.7.1.2
 Baseline study visit
**

**4.**
* Written informed consent*: Potential participants who meet the study eligibility criteria will provide written informed consent during enrolment to the study at baseline study visit.

**5**
* Demographic and lifestyle data (self-reported)*: Age; self-reported sex; gender identity, ethnicity; educational attainment; employment status; socioeconomic status measured using the Townsend Deprivation Index; smoking status.

**6.**
* Alcohol Use Disorders Identification Test, AUDIT (Saunders
*et al*., 1993)*: Validated questionnaire to assess alcohol use.

**7.**
* Past psychiatric history*: Data including age of onset, number and timing of episodes of depression, hypomania and mania will be collected. This is to gain a full understanding of the participant’s clinical history.

**8.**
* Assessment of past and present medication use*: To be used as variates in future analyses.

**9.**
* Retrospective Assessment of the Lithium Response Phenotype (Alda) Scale (
Grof *et al*., 2002)*: Validated questionnaire to retrospectively assess lithium response phenotypes in bipolar disorder participants.

**10.**
* Pittsburgh Sleep Quality Index (PSQI) (
Buysse *et al*., 1989)*: Validated questionnaire which assesses sleep quality and sleep disturbance.

**11.**
* Munich Chronotype Questionnaire (MCTQ) (
Roenneberg *et al*., 2003)*: Validated questionnaire to assess chronotype, collecting information about sleep and wake under natural conditions, including sleep and wake timings.

**12.**
* Modified Seasonal Pattern Assessment Questionnaire (m-SPAQ) (modified from Rosenthal
*et al*., 1984)*: Validated questionnaire to assess impact of seasons on mood and day-to-day life. The questionnaire is modified with the addition of several questions relating to bipolar disorder symptoms and seasonality, the results of which will not be aggregated into the SPAQ scoring system.

**13.**
* WHODAS 2.0 Questionnaire (
Measuring Health and Disability, 2010;
Ustün *et al*., 2010)*: Validated assessment instrument for health and disability, covering six domains of functioning: cognition, mobility, self-care, getting along, life activities, and participation.

**14.**
* 12-days of Sleep Diary*: For the 10 days prior to the overnight CRF study, and for the duration (2 days) of the overnight CRF study, participants will be required to complete a sleep diary to collect data on their sleep and wake timings.

**15.**
* 12-days of 24-hour actigraphy*: For the 10 days prior to the overnight CRF Study, and for the duration (2 days) of the overnight CRF study, participants will be required to wear a wristband actigraphy device (Axivity, UK) to measure their wake and sleep rhythms and wake activity levels.

**16.**
* 12-days of daily light exposure levels* (including daylight exposure on first study day): For the 10 days prior to the overnight CRF Study, and for the duration (2 days) of the overnight CRF study, estimates of light exposure will be derived from the AX3 actigraphy device (Axivity, UK) and ActLumus light logger (Condor Instruments, Brazil) respectively.

**3.7.1.3
 Part A
**

**17.**
* Pregnancy test*: Upon arrival to the Part A appointment, participants of childbearing potential (between the stages of menarche and menopause) will be required to complete a pregnancy test to confirm that they are not pregnant prior to their ingestion of the telemetric pill.

**18.**
* Heart rate, blood pressure, height and weight measurement*

**19.**
* Cannulation:* Venous cannulation of hand or arm for blood sampling over the two nights.

**20.**
* Blood sample collection:* A maximum of 31 blood samples (approximately 60mls total) will be taken over the course of the overnight stay:

1 sample: for lithium level testing (2mls) (only BD on Lithium group)1 sample: for retinal organoid research (Helios-BD Work package 1) (8mls, EDTA Tube), if the participant has consented to their blood samples being used in future ethically approved studies12 samples: twelve blood samples (2.5mls each) taken at hourly intervals between the hours of 7pm and 6am inclusive on Part A Study Day 117 samples: twelve blood samples (2.5mls each) taken at hourly intervals between the hours of 7pm and 6am inclusive on Part A Study Day 2. An additional five blood samples will be taken at 15 minute intervals around the light stimulation protocol (30 minutes prior, 30 minutes during, 30 minutes after).

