Blood sampling will be performed hourly at night to cover a period before and after the light exposure, for measurement of melatonin levels (1900h – 0600h). For the 90 minutes surrounding the light stimulation protocol (30 minutes prior, 30 minutes during, and 30 minutes post), blood samples will be collected at 15-minute intervals. If at any point overnight it is no longer possible to use the cannula to obtain venous blood samples, up to 4 venous blood samples can be obtained via venepuncture. Samples will be centrifuged and blood plasma will be deep frozen until melatonin radioimmunoassay analysis.

If the participant cannot complete the light stimulation protocol at the scheduled time due to an unforeseen issue (e.g. side effects from eye drops), the light stimulation protocol can be attempted/re-attempted within 1 hour of the scheduled time, at the discretion of the research staff, without needing to re-administer eye-drops. If light exposure is commenced but it is not possible to complete the full 30 minutes of exposure, the rest of the protocol procedures (e.g. blood sampling) will still be completed as planned (if possible). Light exposure will not be reattempted once the participant has been exposed to light, even if this is for a short period.

Study Day 3

On Study Day 3, participants can rise and turn on the lights at any time of their choosing from 0600h onwards. Their venous cannula will be removed and participants will be allowed to leave the Clinical Research Facility and go home. Due to the pupil dilation and disrupted sleep period, participants will be advised not to drive on Study Day 3 if they feel their vision has not returned to normal and it is unsafe to drive. Taxi transport will be provided if participants are unable to take public transport home.

After these assessments, all participants will be clinically assessed on the phone or via video call within 3 days to ensure that they have not experienced significant manic or depressive symptoms.

**3.4.4.3
Part B: Retinal assessments
**

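### The stated Part A blood total of about 60 mL covers only the 24 hourly melatonin samples; the 31 listed samples come to at least 70 mL

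*Protocol article*

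**What the plan says.** Section 3.7.1.3 (Part A), item 20, opens with a count and a volume: "A maximum of 31 blood samples (approximately 60mls total) will be taken over the course of the overnight stay". It then lists the components:

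- One 2 mL sample for lithium level, in the lithium group only.
- One 8 mL sample for retinal organoid research, if the participant has consented to future use.
- On night 1, "twelve blood samples (2.5mls each) taken at hourly intervals".
- On night 2, seventeen samples: "twelve blood samples (2.5mls each) taken at hourly intervals between the hours of 7pm and 6am inclusive on Part A Study Day 2", followed by "An additional five blood samples will be taken at 15 minute intervals around the light stimulation protocol". No volume is attached to these five.

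Section 3.7.2 repeats the counts: 31 at most, 30 in the control and non-lithium groups, and 29 for melatonin.

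Section 3.4.4.2 (Study Day 2) describes night 2 as hourly sampling with a denser period around the light. Over 90 minutes, from half an hour before the light starts to half an hour after it ends, "blood samples will be collected at 15-minute intervals". The light itself starts 90 minutes before each participant's estimated temperature nadir (section 3.4.4.2, and item 24 of section 3.7.1.3), so its clock time differs between participants.

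**The concern.** A total and the list it summarises stand in the same item and disagree. The melatonin samples with a stated volume use up the whole 60 mL, which leaves nothing for the two other tubes or the five extra draws.

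Blood volume over two consecutive nights of cannulation is a burden figure that an ethics committee and a participant would read. If it is understated, anyone completing the listed schedule exceeds the protocol's own total.

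There is a second, smaller difficulty. Section 3.4.4.2 spreads 15-minute sampling over 90 minutes, but item 20 allows only five draws beyond the hourly ones. Five draws at 15-minute spacing span 60 minutes. Whether five are enough therefore depends on how the window meets the hourly grid, and neither section says. Staff need one schedule here, because these samples feed the Part A primary outcome (section 3.10.1.1).

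**Working it through.** **Inputs (item 20).** Night 1: 12 × 2.5 mL. Night 2: 12 × 2.5 mL plus 5 × *v*, where *v* is not stated. Lithium tube: 2 mL. Stored tube: 8 mL.

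**Count.** 1 + 1 + 12 + 17 = 31. Without the lithium tube it is 30, and melatonin alone is 12 + 17 = 29. All three agree with section 3.7.2.

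**Where 60 mL comes from.** 24 × 2.5 = 60.0 mL. The stated total equals the hourly samples alone. It appears to leave out seven of the 31 samples: the lithium tube, the stored tube and the five extras.

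**Total for all 31 samples.** 60 + 2 + 8 + 5*v* = 70 + 5*v*. This cannot equal 60 for any *v* of zero or more. The volume of the extras is an assumption, so the range is shown:

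| Participant | *v* = 0 (lower bound) | *v* = 1 mL | *v* = 2 mL | *v* = 2.5 mL | Excess over 60 at *v* = 2.5 |
|---|---|---|---|---|---|
| Lithium and stored tubes | 70.0 | 75.0 | 80.0 | 82.5 | 22.5 (37.5%) |
| Stored tube only | 68.0 | 73.0 | 78.0 | 80.5 | 20.5 (34%) |
| Lithium tube only | 62.0 | 67.0 | 72.0 | 74.5 | 14.5 (24%) |
| Neither tube | 60.0 | 65.0 | 70.0 | 72.5 | 12.5 (21%) |

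**Reverse check.** For 31 samples to total 60 mL, the 29 melatonin samples would have to average (60 − 10) / 29 = 1.72 mL, against the 2.5 mL given for the hourly ones.

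**Window draws.** The window runs from 30 minutes before light-on to 60 minutes after it. At 15-minute steps that is 90/15 + 1 = 7 time points with both ends sampled, or 6 with one end left out. The samples outside night-2 melatonin number 12 + 1 + 1 = 14. If the whole window falls within the 19:00 to 06:00 sampling period, the total depends on the reading:

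| Reading | Total samples |
|---|---|
| 7 points, all hourly draws kept | 31 if light starts at :00, :15 or :30; 32 at :45; 33 at any other minute |
| 7 points, replacing hourly draws inside the window | 31 for starts from :00 to :30; 32 for :31 to :59 |
| 6 points, all hourly draws kept | at most 32 |
| 6 points, replacing hourly draws inside the window | at most 31 |

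The document does not say which reading is meant.

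**The case against.** The best defence on volume is that the total is labelled approximate, that the extras have no stated volume, and that two of the tubes are conditional. What stands of this is a limit on the size. The 82.5 mL figure rests on an assumed 2.5 mL per extra sample and applies only to lithium participants who consent to storage. A reader might infer that every participant exceeds the stated total by more than a third. The documents do not support that: with neither tube the excess is about 21% even at 2.5 mL per extra, and it is smaller if the extras are smaller. The defence does not rescue 60 mL as the total for 31 samples, because the stated volumes alone reach 70 mL.

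On the count, the defence is stronger. Item 20 fixes five additional samples, its list adds to 31, and section 3.7.2 agrees throughout. A reader might infer from the 90-minute window that 31 is wrong and that the true maximum is 33 samples (87.5 mL at 2.5 mL each). That follows on only one of the four readings above, and on another the count never exceeds 31. A reader might also infer that staff would drop window samples to stay within 31, but nothing in the text tells them to.

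It is also fair to say that no safety limit or stopping rule is tied to 60 mL, and that the participant information is not shown, so an error there is only a possibility to check.

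**Conclusion.** The stated volume is wrong as written. About 60 mL is the sum of the 24 hourly melatonin samples, not of the 31 samples it is said to cover. From stated volumes alone the 31 samples come to 70 mL, which is 10 mL over, before the five extras. Assuming 2.5 mL per extra, the totals run from 72.5 mL (neither conditional tube) to 82.5 mL (both tubes).

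The sample count is a lesser matter. The maximum of 31 is consistent with the document's own list and is not shown to be wrong. What is missing is a statement of which time points make up the 90-minute window and whether they add to or replace the hourly draws. Five extras cover that window only if hourly draws coincide with window draws or are replaced by them, and the individually timed light start does not guarantee coincidence.

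This concerns the burden and consent figure and the clarity of the sampling schedule. It does not bear on power or on the method of analysis.

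**What to change.** 1. In item 20, state the volume of each of the five extra samples.
2. Correct either the total or the per-sample volumes so that they agree, and say which participants the total applies to (with or without the lithium and stored tubes). The documents do not show which figure is the intended one.
3. Check the participant information for the same total and correct it if it appears there.
4. Reconcile sections 3.4.4.2, 3.7.1.3 (item 20) and 3.7.2: list the window time points relative to light-on, say whether they add to or replace hourly draws inside the window, and confirm the resulting maximum. This needs no change to how the light is timed.

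The cost is a minor amendment of a few lines and, if the participant information carries the figure, a corrected sheet.

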**21.**
* Ingestion of eCelsius telemetric temperature pill:* To measure core body temperature over 10 hours on the night of Study Night 1 for calculation of core body temperature nadir.

**22.**
* Overnight Sleep Study Protocol:* Participants will be required to complete 2 sequential overnight stays at the Clinical Research Facility, Royal Infirmary of Edinburgh. During the Overnight stay, participants will be exposed to dim light conditions (<5 lux) from arrival until 2200h, and dark conditions between the hours of 2200h and 0600h.

